### Study design

3.1

The **p**ilot study on **A**ngled **M**anual **T**raction and usua**L** car**E** for cervical **R**adiculopathy (pAMTLER) will be an open-label RCT with two parallel groups and blind evaluation. In this five-period (7 days per period) trial with a total of 15 visits, 48 eligible participants with CR will be enrolled. All enrolled participants will receive usual care for four periods. The 24 participants randomly assigned to the experimental group will also receive 14 sessions of AMT. The baseline will be defined as the pre-treatment assessment during the initial visit in the first period after randomization. Participants will be scheduled to complete the outcome assessments prior to treatment during the initial visit in each period. Figure 1 illustrates the study design. The pAMTLER will be conducted at the Guangdong Provincial Hospital of Chinese Medicine (GPHCM), Guangzhou, China, with approval from the Ethics Committee at GPHCM (approval number: BF2024-156-01). The study protocol was registered with ChiCTR2400087289, and is reported according to the Standard Protocol Items: Recommendations for Interventional Trials (SPIRIT) (31) (Appendix S2). Figure 2 overviews the participant flow and details the assessed content at each scheduled visit (Appendix S3).

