### Recruitment

3.3

Potential participants will be recruited by clinicians at GPHCM’s orthopedic outpatient clinics, as well as through advertisements issued via GPHCM’s official accounts, social media platforms including TikTok and WeChat (Tencent), and newspapers. Interested individuals will be encouraged to contact the researcher (a registered research physician responsible for usual care), using the private telephone line listed on the recruitment flyers in clinic or the advertisements. The research physician will be independent of the outcome assessment and random allocation process. He will identify candidates who fulfill the CR diagnostic criteria among the approached individuals, and invite them to participate in the pAMTLER after informing them of the study’s purpose, procedure, as well as participation benefits and potential risks. Willing candidates will be further assessed for eligibility according to the inclusion and exclusion criteria after voluntarily signing written informed consent forms. Those eligible to participate in the post-evaluation will then be consecutively enrolled and randomized. The randomized individuals can withdraw participation consent at any time during the trial without prejudice. Details related to screening, enrolment, withdrawal, and reasons for non-participation will be documented in a prearranged register.

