### Randomization and blinding

3.4

Eligible participants will be assigned to either the experimental group (AMT add-on) or the control group (usual care alone) at a 1:1 ratio with a random allocation schedule, which will be generated by a third-party biostatistician using R software (version 4.3.0). The treatment allocation table will be stratified by baseline cervicobrachial pain level (NRS < 7 or ≥ 7) and sex, then randomized with varying block sizes to avoid insufficient concealment caused by limited sample size. The random allocation schedule will be concealed in sequentially numbered, sealed, opaque envelopes, and managed by the biostatistician. He will reveal the treatment allocation via phone according to the participants’ enrolment sequences.

Due to the nature of the intervention, it will be impossible to blind the participants and treatment providers. However, outcome assessors, data managers and statistical analysts will be unaware of the treatment allocations.

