#### Data analysis

3.7.2

Data will be statistically analyzed using PASW Statistics 18.0, STATA 14.0 and R 4.3.0. Continuous variables will be summarized as means with standard deviations or medians with interquartile ranges, whereas categorical variables will be presented as counts and percentages. The primary outcome will be outlined using descriptive statistics. Building on reported positive associations between colder temperatures, male sex, and more consultations for musculoskeletal pain (76), we will conduct subgroup analyses to explore how season and sex influence enrolment, retention, and adherence, thereby informing weather-adaptive management strategies for the future full RCT. Secondary outcome measures will be analyzed based on the intention-to-treat population approach. Any post-randomization participants who received at least one intervention session will be included in the full analysis set. Among these, those who completed at least 80% of the planned treatments without any significant protocol violations will be categorized into the per-protocol analysis set. Any post-randomization participants receiving at least one intervention session will be classified into the safety analysis set. Any missing data will primarily be handled using multiple imputation, with last observation carried forward applied for sensitivity analysis.

We will analyze both within- and between-group changes for each efficacy-related secondary outcome variable using a linear mixed-effects model to derive estimates of intervention effects.

Group allocation, time-point and the interaction between group allocation and time-point will act as fixed-effects, individuals as random effects, and baseline measurements as covariates. Given that this exploratory trial is not formally powered to assess effects, a recommended confidence interval of 75% will be employed to infer the size and direction of the calculated effect estimates (77). The 75% confidence interval will be compared with the MCIDs to preliminarily assess whether the difference between treatment groups holds potential for clinical significance (77). The remaining secondary outcome measures involving AER, ARR, and intervention costs, as well as baseline variables, will be presented descriptively by the groups.

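### Baseline self-reports are taken after randomisation in an open-label trial, with nothing stated to keep allocation from the participant first, and they then serve as model covariate and starting point for change

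*Protocol article*

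**What the plan says.** On timing, Section 3.1 (Study design) of the protocol article states: "The baseline will be defined as the pre-treatment assessment during the initial visit in the first period after randomization". It adds: "Participants will be scheduled to complete the outcome assessments prior to treatment during the initial visit in each period". Section 3.3 (Recruitment) puts consent and the eligibility check first, and then: "Those eligible to participate in the post-evaluation will then be consecutively enrolled and randomized". It places no efficacy assessment before randomisation, apart from the pain score needed for eligibility.

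On disclosure, Section 3.4 (Randomization and blinding) says of the biostatistician: "He will reveal the treatment allocation via phone according to the participants’ enrolment sequences". It does not say who takes the call or when the participant is told. It also says: "Due to the nature of the intervention, it will be impossible to blind the participants and treatment providers". Outcome assessors, data managers and analysts are blinded.

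On use, Section 3.7.2 (Data analysis) fits a linear mixed-effects model with group, time and their interaction as fixed effects, "individuals as random effects, and baseline measurements as covariates", and analyses changes within and between groups. The resulting 75% intervals are compared with MCIDs.

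On the word baseline, Section 3.4 has the allocation table "stratified by baseline cervicobrachial pain level" (below 7, or 7 and above) and by sex. That value has to exist before randomisation.

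**The concern.** A covariate is a safe baseline when allocation cannot have influenced it. Here the NRS, NDI, QuickDASH, EQ-5D-5L, WPAI: CR, SDS and SAS are completed after randomisation by people who may already know their arm. Disappointment at usual care alone, or anticipation of AMT, could move the reported scores differently in the two arms before any treatment is given. The model would then adjust for a difference that allocation itself produced, and change from baseline would start from it.

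Blinded assessors do not protect a self-report. The Discussion concedes that unblinding may bias self-reported measures, but its safeguards (separate rooms, therapist and research physician kept out of assessment) do not deal with the timing of the baseline. The same section expects unbiased effect estimates to inform the power calculation of the definitive trial. Participant blinding during follow-up is out of reach, whereas the baseline can be protected by order alone.

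**Working it through.** The plan gives no figure for this point, so there is none to reproduce. The check has two parts.

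**1. The sequence.** Reading Sections 3.1, 3.3 and 3.4 together: consent, eligibility (including NRS of 4 or more over the previous 24 h, Section 3.2), randomisation with allocation revealed by phone, then baseline assessment, then first treatment. The text contains no step that withholds allocation until baseline is complete. The pain value that defines the stratum precedes randomisation, and the value that Section 3.1 calls baseline follows it. They are therefore two measurements. If the stratum uses the eligibility score, they also differ in recall: previous 24 h for eligibility, time of evaluation for the outcome NRS (Section 3.6.2).

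**2. The possible size.** From the article: 24 per arm and 75% intervals. Assumed, because the article gives none: NRS SD of 2 points; baseline-to-follow-up correlation of 0.3, 0.5 or 0.7 (equal to the slope b when SDs are equal); reported baseline in the AMT arm shifted by d = 0.5 or 1.0 point relative to control. The model is simplified to one follow-up with baseline adjustment, and the true effect is set to zero.

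If only the baseline report is shifted:

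- bias in the adjusted effect = −b × d
- bias in the difference in change scores = −d
- 75% half-width ≈ 1.150 × 2 × √(1 − b²) × √(2/24)

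Results from 6,000 simulated trials per setting:

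| b | d | Adjusted bias, formula | Adjusted bias, simulated | Change-score bias, simulated | 75% half-width | Actual coverage |
|---|---|---|---|---|---|---|
| 0.3 | 0.5 | −0.15 | −0.166 | −0.520 | 0.634 | 0.723 |
| 0.3 | 1.0 | −0.30 | −0.277 | −0.975 | 0.634 | 0.703 |
| 0.5 | 0.5 | −0.25 | −0.243 | −0.496 | 0.575 | 0.698 |
| 0.5 | 1.0 | −0.50 | −0.501 | −0.999 | 0.575 | 0.550 |
| 0.7 | 0.5 | −0.35 | −0.342 | −0.490 | 0.474 | 0.607 |
| 0.7 | 1.0 | −0.70 | −0.698 | −1.001 | 0.474 | 0.316 |

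With d = 0, coverage is 0.734 to 0.749. With a covariate recorded before allocation is known, the mean adjusted effect stays within 0.023 of zero in every setting.

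*Direction.* Lower NRS is better. If AMT participants report higher baseline pain than controls, the bias is negative and flatters AMT. If controls report higher, the sign reverses and AMT's benefit is understated.

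*If the shift persists.* Suppose the same shift d also enters the follow-up reports. A pre-allocation covariate then leaves bias d, a post-allocation covariate leaves d − b × d = (1 − b)d, and the change score leaves d − d = 0. With b = 0.5 and d = 0.5 these are 0.50, 0.25 and 0.

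*Variability.* Adding a constant to every report in one arm leaves the within-arm SD unchanged, and with arm in the model it leaves the residual variance unchanged.

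**The case against.** The strongest reply is that contamination is inferred. The mechanism needs the participant to know the arm before answering, and the article does not say when that happens. The visit schedule in Figures 1 and 2 and the appendix, and the procedures for enrolment and outcome evaluation mentioned in Section 3.8, are not shown. This stands: a reader might infer that the baseline is biased, but the text supports only that it is not stated to be protected.

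Second, the trial is a pilot. Its success criteria are enrolment, adherence and retention, and none uses this covariate. Efficacy is secondary and acknowledged to be unpowered. This also stands, and it limits the point to the secondary estimates.

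Third, a reader might infer that a pre-allocation baseline makes the efficacy estimates unbiased. It does so only if allocation knowledge leaves follow-up reports alone. Under a persisting shift, the pre-allocation covariate shows the largest of the three biases. That is not a reason to keep the present order: the cancellation depends on an unknown shift staying constant, and follow-up reporting bias is a separate limitation that the Discussion already concedes.

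Fourth, a reader might infer that the variability estimates for the next trial are spoiled. A constant shift between arms does not change them.

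Fifth, it is tempting to substitute the pre-randomisation NRS as main covariate for all pain outcomes. The eligibility score covers cervicobrachial pain over the previous 24 h, whereas the pain outcomes include neck, shoulder and upper-extremity pain, all rated at the time of evaluation. It suits a sensitivity analysis for cervicobrachial pain only.

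**Conclusion.** The point holds as an unguarded and avoidable route for bias in the secondary, mostly self-reported efficacy outcomes. It is not evidence that bias has occurred.

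Under the assumptions above, the adjusted effect would be off by 0.15 to 0.70 NRS points. A 1-point shift amounts to about half to one and a half 75% half-widths (0.30/0.634 = 0.47; 0.70/0.474 = 1.48). Against the 2-point criterion for meaningful relief in Section 3.6.2, 0.25 points is one eighth and 0.70 about one third. The shift, slope and SD are all assumed; the real size and sign are unknown, and AMT could be made to look worse rather than better. Grip strength is not a self-report and is less exposed.

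The primary feasibility rates are unaffected and the variability estimates are not materially affected. Separately, and whether or not any bias arises, Sections 3.1 and 3.4 use one word for two different pain values and need to be reconciled.

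**What to change.** For participants still to be randomised:

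- Complete all efficacy questionnaires and grip strength after consent and confirmed eligibility, but before allocation is disclosed.
- Define that assessment as baseline in Section 3.1.
- Give the pre-randomisation NRS used for stratification its own name in Section 3.4, with its recall period.

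For participants already randomised:

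- Report whether the baseline assessment came before they knew their arm.
- Keep the recorded baseline in the main model, since no other baseline is described for the non-pain scales.
- Add a sensitivity analysis for cervicobrachial pain with the pre-randomisation NRS as covariate, noting that the eligibility score covers the previous 24 h whereas the outcome is pain at the time of evaluation.

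The cost is a reordering of existing assessments and a change of wording, with no new instrument. The benefit is partial: the Results section reports 33 patients recruited by 31 July 2025, so if all were randomised only 48 − 33 = 15 remained at that date. The downside is that baseline timing will differ between earlier and later participants, which must be disclosed. The definitive trial should adopt the corrected order from the start.

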**Figure 1 fig1:**
[figure not shown]
pAMTLER study design. CR, cervical radiculopathy; R, randomized allocation; CG, control group; EG, experimental group; V, visit; Peri, period; NRS-CP_p24_, having cervicobrachialgia over the previous 24 h on NRS; +1 d, data premitted to be collected within 1 day after the scheduled time. 

 collecting data on efficacy- and cost-related outcome measures, followed by administering AMT; 

, collecting data on cost-related outcome measures, followed by administering AMT; 

, collecting data on efficacy- and cost-related outcome measures; 

, recording adverse events, adverse reactions and concomitant medication during the trial; 

, receiving usual care for 4 periods. Baseline assessment including socio-demographics (age, sex, education level, employment status, health insurance, etc.), medical history (comorbidities, concomitant medications, details related to the cervicobrachial pain episode, etc.) and physical examination (dominant hand, abnormal deep tendon reflexes, radiculopathy level shown on magnetic resonance imaging, etc.).

**Figure 2 fig2:**
[figure not shown]
pAMTLER SPIRIT schedule. AR, adherence rate; DR, drop-out rate; RR, retention rate; CRE, completion rates of efficacy-related outcome measures; CRC, completion rates of cost-related outcome measures; NRS, cervicobrachial pain, upper extremity pain and numbness, neck pain, and shoulder pain graded by the numeric rating scale; QuickDASH, quick disabilities of the arm, shoulder, and hand questionnaire; NDI, neck disability index; analgesics consumption, NSAID consumption per period and opiate consumption per period; WPAI-CR, work productivity and activity impairment questionnaire: cervical radiculopathy; EQ-5D-5L, euroqol 5-dimensional descriptive system; SDS, Zung’s self-rating depression scale; SAS, Zung’s self-rating anxiety scale; AER, adverse event rates; ARR, adverse reaction rates; DMC, direct medical costs; DnMC, direct non-medical costs. In baseline assessment, socio-demographics (e.g., age, sex, education level, employment status, health insurance), medical history (e.g., comorbidities, concomitant medications, details related to the cervicobrachial pain episode), physical examination (e.g., dominant hand, abnormal deep tendon reflexes) and radiculopathy level are shown on magnetic resonance imaging.

### Study population

3.2

Participants having all of the following conditions will be included:

Satisfied the following diagnostic criteria of CR, which was drafted according to the *Expert Consensus on Cervical Radiculopathy Standardized Diagnosis and Treatment* issued in China in 2015 (32), the *Diagnosis and Treatment of Cervical Radiculopathy from Degenerative Disorders* released by the North American Spine Society in 2010 (7), and pertinent literature about CR diagnostic accuracy (33):
suffering from cervicobrachialgia, accompanying numbness, weakness, and abnormal deep tendon reflexes in the upper limb(s).having positive provocation tests such as Spurling’s test, distraction test, or brachial plexus tension test.pathologic level indicated by symptoms and signs in line with the impinged cervical nerve roots shown on magnetic resonance imaging.
Aged ≥ 45 to ≤ 75.cervicobrachialgia over the previous 24 h ≥ 4 on numerical rating scale (NRS)No AMT experience.Signed informed consent.

Participants with any of the following phenomenon will be excluded:

Comorbidities that could contribute to cervicobrachialgia (e.g., shoulder bursitis, thoracic outlet syndrome, spinal muscular atrophy, cubital tunnel syndrome, tennis elbow, carpal tunnel syndrome, angina pectoris and pathological changes of cervical vertebrae like tuberculosis, neoplasms).Congenital spine diseases (scoliosis, abnormalities, etc.), cervical surgery history, spinal cord injury history, osteomyelitis, severe osteoporosis or any other types of cervical spondylosis (cervical myelopathy, mixed-type cervical spondylosis, etc.).Contraindications against NSAIDs or opiates (e.g., hypersensitivity to NSAIDs or opiates, active or relapsing peptic ulcer or gastrointestinal bleeding, NSAID-related gastrointestinal bleeding or perforation, gastrointestinal obstruction, hepatic failure, renal failure with glomerular filtration rate <15 mL/min/1.73 m^2^, heart failure with New York Heart Association class IV, bronchial asthma, and on prescribed monoamine oxidase inhibitors within 2 weeks).Active malignancy.Planning surgery during the study period.Failing to understand and/or follow the study protocol due to disabilities (blindness, deafness, dumbness, intellectual disability, psychiatric disorder, etc.).Gravida, lactating women, or individuals planning to conceive during the trial.Participating in other clinical trials within 1 month or planning to participate in other concurrent clinical studies.Any other conditions investigators deem inappropriate.

### Recruitment

3.3

Potential participants will be recruited by clinicians at GPHCM’s orthopedic outpatient clinics, as well as through advertisements issued via GPHCM’s official accounts, social media platforms including TikTok and WeChat (Tencent), and newspapers. Interested individuals will be encouraged to contact the researcher (a registered research physician responsible for usual care), using the private telephone line listed on the recruitment flyers in clinic or the advertisements. The research physician will be independent of the outcome assessment and random allocation process. He will identify candidates who fulfill the CR diagnostic criteria among the approached individuals, and invite them to participate in the pAMTLER after informing them of the study’s purpose, procedure, as well as participation benefits and potential risks. Willing candidates will be further assessed for eligibility according to the inclusion and exclusion criteria after voluntarily signing written informed consent forms. Those eligible to participate in the post-evaluation will then be consecutively enrolled and randomized. The randomized individuals can withdraw participation consent at any time during the trial without prejudice. Details related to screening, enrolment, withdrawal, and reasons for non-participation will be documented in a prearranged register.

### Randomization and blinding

3.4

Eligible participants will be assigned to either the experimental group (AMT add-on) or the control group (usual care alone) at a 1:1 ratio with a random allocation schedule, which will be generated by a third-party biostatistician using R software (version 4.3.0). The treatment allocation table will be stratified by baseline cervicobrachial pain level (NRS < 7 or ≥ 7) and sex, then randomized with varying block sizes to avoid insufficient concealment caused by limited sample size. The random allocation schedule will be concealed in sequentially numbered, sealed, opaque envelopes, and managed by the biostatistician. He will reveal the treatment allocation via phone according to the participants’ enrolment sequences.

Due to the nature of the intervention, it will be impossible to blind the participants and treatment providers. However, outcome assessors, data managers and statistical analysts will be unaware of the treatment allocations.

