The TMG assumes responsibility for day-to-day trial operations. It will consist of a project manager, a registered research physician, a registered therapist, a trial coordinator, two research assistants and a data manager. All members will attend a pre-trial training workshop to familiarize themselves with the trial implementation process, and to ensure adherence to the study protocol and standard operating procedures. The trial coordinator is to formulate follow-up programs based on the study protocol. They will keep in touch with participants to facilitate their attendance at scheduled follow-ups, but also to assist in promptly detecting any AE. The research assistants will collect and record data on paper case report forms (CRF), including participants’ socio-demographics (age, sex, education level, employment status, health insurance, etc.), medical history (comorbidities, concomitant medications, details related to the cervicobrachial pain episode, etc.) and physical examination at baseline (dominant hand, abnormal deep tendon reflexes, radiculopathy level shown on magnetic resonance imaging, etc.) and discharge (abnormal deep tendon reflexes), secondary outcomes, treatment information, and adverse event details. Data may be collected within 1 day after the scheduled time. Unless they explicitly refuse, research assistants will follow up with any withdrawn participants to acquire data until the trial end. Additionally, they will track any AE from reporting until resolution. The data manager will regularly monitor data quality, working with research assistants to recover missing data and clarify ambiguous data to ensure all reported data are accurate, complete, legible and verifiable from source documents. Research assistants will double-enter the data from the paper CRF after monitoring into an Epidata-based electronic data capture system. Any discrepancies from double entry will be verified against the paper CRF. The data manager will lock the electronic data capture after all data have been cleaned; researchers will be unable to modify the data. The TMG will meet weekly to review study progress during the trial. The project manager will meet with the TSC biweekly to align on key decisions.

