## Discussion

5

A full RCT with appropriate power is necessary to establish the clear effects of AMT on pain relief and functional improvement in patients with CR. However, such studies conducted over the past decade have been insufficient. Therefore, establishing whether a more extensive future RCT would be viable is of paramount importance (78). The pAMTLER study is a randomized pilot developed to address this issue. It will focus on assessing the ability to enroll CR individuals with moderate-to-severe cervicobrachialgia, to retain participants for the intervention duration, and to encourage participants to adhere to the protocol during the trial, thereby establishing the feasibility of a proposed full-scale RCT. Meanwhile, the pAMTLER study can provide preliminary data on the efficacy and safety of AMT for CR, thereby complementing the key estimates regarding outcome variability necessary for sample size calculations in the confirmatory trial.

Several advantages make the pAMTLER study instructive for a future definitive RCT on AMT for CR. To begin, the pAMTLER study meets the methodological requirements for feasibility and pilot projects. It was carefully designed, not only with adequate randomization, allocation concealment, and blinding of outcome assessors and statisticians, but also specifying clear feasibility objectives, analytic plans, and criteria for the success of feasibility (80). Additionally, with small feasibility study samples, confidence intervals for clinically important differences in outcomes of interest are narrowed to a 75% confidence level. Such analytical strategies are justified, contributing to realistic and unbiased effect estimates to inform subsequent power calculation for the future full definitive RCT (77, 79). Third, unlike most previous RCTs which directly compare different multimodal conservative strategies for CR patients (20, 81), the pAMTLER study is characterized by a randomized add-on trial. An add-on study design could be more rational in circumstances where analgesics are commonly preferred as the first-line therapy (82), while also allowing for further understanding of AMT’s superiority in real-world clinical practice of CR.

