However, there are still limitations that should be disclosed. The first is failing to blind the participants, the therapist and the research physician. Since most outcomes are measured using patient self-reported instruments, the fact that these individuals remain unblinded may introduce measurement bias. To address this, participants in each arm will be escorted by a trial coordinator to a dedicated clinic room for visits and interventions. The therapist will be barred from contact with control-arm participants and from outcome-related data collection or evaluation; the research physician, remaining neutral, will inquire only about pain improvement and will likewise refrain from any outcome-related assessment. To reduce selection bias arising from the unmasked research physician, a structured eligibility screening process will be implemented. Also, the research physician will be isolated from intervention allocation. The inability to conduct a process evaluation to further assess the fidelity, adherence, contextual factors, implementation facilitators of and barriers to AMT and usual care following the initiative might represent another limitation. Given the constrained research funding for the pAMTLER, a process evaluation will be conducted in parallel with the future well-funded full-scale RCT.

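### The article claims blinded outcome assessors and data manager, but the duties it gives these staff include records that show the arm

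*Protocol article*

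**What the plan says.** Section 3.1 describes an open-label trial with blinded evaluation. Section 3.4 concedes that participants and treatment providers cannot be blinded, then says that "outcome assessors, data managers and statistical analysts will be unaware of the treatment allocations". The Discussion lists "blinding of outcome assessors and statisticians" among the design strengths.

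Section 3.8 describes who handles the data. The research assistants complete the paper case report forms (CRFs), and the items they record include "secondary outcomes, treatment information, and adverse event details". Also, "Research assistants will double-enter the data from the paper CRF". For the next role, "The data manager will regularly monitor data quality, working with research assistants to recover missing data and clarify ambiguous data", with the aim that the data can be verified from source documents. The assistants and the data manager belong to a management group that also includes the therapist and the research physician and that meets weekly.

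The Discussion, describing steps against measurement bias, adds that "participants in each arm will be escorted by a trial coordinator to a dedicated clinic room for visits and interventions".

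**The concern.** An assessor stays blinded only if the tasks given to that person do not disclose the arm. Here, the staff who record outcomes also record what treatment was given, and the person responsible for data quality reviews both. In an add-on trial against usual care alone, a treatment record is in effect an allocation record.

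Two things are at stake. Outcomes that depend on staff conduct or judgement can be influenced by knowledge of the arm. In addition, the report would credit the pilot with a protection that its described organisation does not provide, and the full-scale trial could inherit the same procedures.

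**Working it through.** The plan states no figure to reproduce. The check sets the blinding claim beside the duties.

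1. **Who assesses outcomes?** The article does not name the assessors, so this goes by elimination. The research physician is kept out of outcome assessment (3.3, 3.5.1, Discussion). So is the therapist (3.5.2, Discussion). The coordinator arranges and escorts visits. Only the two research assistants are described as recording secondary outcomes (3.8).

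2. **What else do they record?** Section 3.8 places treatment information and adverse event details in the same list of duties. It assigns the list to the assistants jointly and states no split.

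3. **Does that information show the arm?** Section 3.5.2 schedules AMT daily in the first 7-day period, then three, two and two sessions: 7 + 3 + 2 + 2 = 14, the stated total. Efficacy assessments come before treatment at the first visit of each period. The AMT sessions due to be on record by each assessment are therefore:

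| Assessment at start of period | Experimental | Control |
|---|---|---|
| 1 (baseline) | 0 | 0 |
| 2 | 7 | 0 |
| 3 | 7 + 3 = 10 | 0 |
| 4 | 10 + 2 = 12 | 0 |
| 5 | 12 + 2 = 14 | 0 |

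   From the second assessment on, anyone who has seen the treatment record can tell the arm.

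4. **Costs.** Section 3.6.2 has direct costs collected at every visit, and Table 2 lists AMT as a cost item. Section 3.8 does not name cost data among the assistants' duties, so this second route applies only if they collect it.

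5. **Data manager.** This role reviews the CRF data, resolves queries with the assistants and ensures verifiability from source. Treatment information is part of those data, so the claim for this role is in difficulty whoever the assessors are.

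6. **Room.** If the Discussion means a separate room for each arm, the location also reveals allocation. If it means one trial room, it does not. Steps 1 to 5 do not depend on this.

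7. **Which outcomes are exposed?** Of the efficacy measures in 3.6.2, only grip strength is administered by staff. The rest are scales, questionnaires or diary entries completed by unblinded participants. Adverse events are recorded by staff and divided by whether they are associated with the intervention, which requires judgement. The article does not say who makes that attribution.

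8. **How much can still be changed?** By 31 July 2025, 33 of the planned 48 had been recruited (Results): 33/48 = 69%, leaving 48 − 33 = 15, if recruited there means randomised.

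**The case against.** The strongest defence is that the article never says the research assistants are the assessors. Section 3.8 lists outcome evaluation and data collection as separate topics for operating procedures, two assistants could divide the work, and staff-level masking is often left to a full protocol. That stands as a limit: the identification is an inference, and an undisclosed split is possible. It does not remove the conflict, because the article assigns the duties jointly and describes no other outcome recorder. It also does not help the data manager.

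Several stronger readings are tempting but unsupported:

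- **That visits certainly take place in arm-specific rooms.** The wording is singular, can mean one shared room, and is offered as a safeguard.
- **That every assessor necessarily handles arm-revealing pages.** Treatment information is not defined and could include usual-care records common to both arms. The CRF layout is not described.
- **That the weekly meeting unblinds staff.** Its stated purpose is to review progress, and nothing says that individual allocations are discussed.
- **That deep tendon reflexes are a biased outcome.** They are a baseline and discharge examination and not among the listed outcomes.
- **That the feasibility results are compromised.** Enrolment, retention, adherence and completion offer little route for assessor bias.

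It is also fair that grip strength is a dynamometer reading, although encouragement can still affect effort. The Discussion already discloses possible measurement bias from unblinded participants. Its safeguards, however, address the therapist and the physician, not the assistants or the data manager.

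**Conclusion.** The concern holds in a limited form. Sections 3.1, 3.4 and 3.8 and the Discussion cannot all stand as written: the described duties expose the data manager, and on the natural reading the outcome recorders, to information that identifies the arm. The conclusion assumes that the assistants are the assessors and that treatment information includes AMT sessions. It does not depend on the room arrangement.

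The size of any bias cannot be derived from the document. The practical reach is grip strength and the recording and attribution of adverse events, from the second assessment onward. Severity is moderate: the primary outcomes are feasibility measures, and the efficacy analyses are exploratory, with 75% confidence intervals. The article's description of its blinding still needs correction.

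**What to change.** **For remaining participants:**
- One existing assistant does only efficacy assessments, before treatment and in an arm-neutral room.
- The other handles treatment, cost and adverse event pages in a separate CRF booklet, which the assessor neither sees nor enters until that participant's last assessment.
- Treatment pages are masked from the data manager, or the blinding claim is dropped for that role.
- The room wording in the Discussion is clarified.

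**For assessments already made:** procedural change cannot restore blinding. Report who assessed outcomes and what they knew of allocation, and qualify the blind-evaluation label in 3.1, the statement in 3.4 and the strength claimed in the Discussion to match.

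**Cost:** no extra staff and a divided CRF, but less flexible cover between the two assistants, later double entry of the separated pages, and a weaker blinding claim in the report.
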